| Study Design The research aims will be addressed with a matched cohort study design.  Two cohorts will be assembled from the CPRD GOLD primary care database:  (1) The exposed cohort will include women diagnosed with a breast cancer (list of Read codes available in appendix 2) after at least 12 months of uninterrupted up-to-standard follow-up in CPRD (to ensure that the breast cancer is an incident event).  (2) A comparison cohort will be assembled by randomly selecting, for each woman with a breast cancer diagnosis, up to 4 women of similar age (3-year range), attending the same GP practice and with at least 12 months of uninterrupted up-to-standard data quality for research, but with no history of cancer at the date of the breast cancer diagnosis of the matched breast cancer patient.  The index date will be the date of breast cancer diagnosis for the exposed group; comparison patients will take the same index date as their exposed match. Please see section L for more details.  Inclusion criteria for both cohorts are: female sex, aged ≥18 years, and having a clinical record with at least 12 months of uninterrupted up-to-standard data quality for research (as measured by CPRD) before the breast cancer diagnosis date (to ensure the cancer record represents incident disease). Exclusions will be the diagnosis of severe mental illness (i.e. organic mental disorder, mental disorders due to substances, schizophrenia, delusional disorders, or manic or bipolar episodes), having a history of the specified mental health outcome in the year before index date; and having had a diagnosis of any other cancer prior to the index date.  All women will be followed from the index date until the earliest date of: outcome observed, a cancer diagnosis, death recorded, transference out of the practice; last data collection for the practice.  Matching will allow close control of key covariates, include GP practice that is difficult to adjust for in a statistical model (too many levels), and has the practical advantage of reducing the size of the comparison group (which might otherwise include several million women) by restricting to the most relevant comparison patients. |

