| Planned use of linked data (if applicable): The following linkages will be requested:  Death registration data from the Office for National Statistics (ONS)  HES Admitted Patient Care (HES-APC)  Index of Multiple Deprivation 2015 (IMD), practice and patient level  Data coming from these data sets will supplement information available in the CPRD GOLD primary care database, but linked data will be used in sensitivity analysis only.  Data from the ONS-mortality and HES-APC databases will be important to increase the completeness and validity of some outcomes. For example, for suicide, only 26% of the suicides registered in the ONS mortality data (gold standard) were captured in CPRD, indicating low sensitivity of this source [28]. Similarly for non-fatal self-harm, only 68% of the cases registered in HES-APC could be identified in CPRD [28]. Of note, patients who had the outcome recorded in the year prior to the index date will be excluded, and thus this finer definition of the outcomes will impact patients’ selection and patients’ who are identified as having had the outcome. Information on the exposure will not be supplemented by data from HES-APC.  Patient-level quintiles of IMD will be used to control for socioeconomic status, which is a major confounder of the association between breast cancer history and adverse mental health outcomes. Even though women in the comparison group are selected from the same primary care practice of the index-case, and thus IMD at practice level will not vary by matched set, the patient-level IMD will allow for a finer adjustment of socioeconomic status. Practice level of IMD is requested to allow us to study effect modification in the full dataset.  We acknowledge that analyses including linked data will be restricted to the subset of practices and patients who consent to the linkage scheme (~75% of the practices in England); the coverage periods for the dataset will be taken into account (see table below). This will result in reductions in sample size and potentially impact the power of the study to reject the null-hypothesis. Thus, these data will be used in sensitivity analysis only.  Table 3 Coverage period of the data included in the databases that will be linked to the CPRD GOLD primary care database.   \| **Database** \| **Coverage period** \| \| --- \| --- \| \| HES Admitted Patient Care (APC) \| April 1997 – December 2017 \| \| ONS death registration \| January 1998 – February 2018 \| |

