| Definition of the Study population Breast cancer cohort  The study population will consist of all adult women recorded in the CPRD GOLD primary care database as having had an incident breast cancer (Read codes provided in appendix 2) diagnosed during up-to-standard follow-up and prior to the most recent version of the CPRD GOLD primary care database available after all approvals have been obtained.  Inclusion criteria:   1. Female sex, aged ≥18 years; 2. Recorded with a breast cancer diagnosis during CPRD follow-up; 3. Clinical record with at least 12 months of uninterrupted up-to-standard data quality for research (as measured by CPRD) before the breast cancer diagnosis date (to ensure the cancer record represents incident disease).   Exclusion criteria:   1. Diagnosis of severe mental illness before the breast cancer diagnosis (i.e. organic mental disorder, mental disorders due to substances, schizophrenia, delusional disorders, or manic or bipolar episodes) (a provisional list of Read codes was defined for feasibility counts); 2. History of the specified mental health outcome in analysis in the year before the breast cancer diagnosis (list of Read codes to be defined in objective 1 of this study); 3. Diagnosis of any other cancer prior to breast cancer (Read codes available from Ranopa et al. [14]). |
| Selection of comparison group(s) or controls Non-cancer comparison cohort  A comparison cohort will be assembled by randomly selecting, for each index case, up to 4 women of similar age (3-year range), attending the same GP practice, but with no history of cancer at the index date. Matching will also consider the eligibility of the patients’ data for linkage, to ensure that matched-sets have the same probability of having had the information recorded when conducting sub-set analysis using linked data. Controls will be selected using nearest neighbour matching methods without replacement [29]. Women in the non-cancer comparison cohort who meet one or more exclusion criteria will be excluded, as well as their index case.  Women diagnosed with breast cancer during the follow up period will be censored from the unexposed group at the date of the cancer diagnosis, but will be eligible to separately contribute in the exposed group from this date (with corresponding unexposed matches). |

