| Exposures, Outcomes and CovariatesExposure: breast cancer Women will be considered exposed at the day of the breast cancer diagnosis (index date), denoted by the first entry of one or more of the Read codes provided in appendix 2. Primary outcomes: anxiety and depression To our knowledge, there is no validated list of Read codes to identify anxiety and depression in the CPRD GOLD primary care database. Algorithms will be developed and tested to identify anxiety and depression cases in CPRD. The algorithms will be chiefly determined by clinical diagnoses of anxiety and depression registered in the EHR with Read codes, and supplemented with information from drug prescriptions, referrals, and symptoms (if deemed suitable). Please see section N, plan of analysis for specific aim 1, for more details on the construction and validation of algorithms. Secondary outcomes: fatigue, mild cognitive impairment, pain, sleep disturbance, sexual dysfunction, and fatal and non-fatal self-harm Similarly, we will develop and test outcome-specific algorithms that identify events using a hierarchy of data on clinical diagnoses, prescriptions, referrals and symptoms.  In sensitivity analysis, we will consider linked data (see section J for data linkage requested) to develop more precise definitions of the outcomes, when possible. For example, two definitions of suicide will be considered: (1) considering Read codes only to identify suicides in CPRD; (2) considering Read codes for suicide as well as death registration data where suicide was recorded as primary cause of death (ICD-10 codes provided in appendix 3) Covariates Variables considered as potential confounders or effect modifiers of the association between breast cancer history and anxiety and depression (the primary outcomes of this study) are described below. The directed, acyclic graph (DAG) in appendix 4 explicitly describes the assumptions of the causal relations between the variables that underpin the choice. Please refer to the data analysis (section N) for details on which variables will be considered for sensitivity analyses only. *Potential confounders*  - Age at diagnosis (categorical variable, in 10-year age bands)   Defined as the absolute difference between the year of breast cancer diagnosis and year of birth. Age is a strong risk factor for breast cancer and for mental disorders.   - Alcohol drinking habits at diagnosis (categorical variable: current drinker, former drinker, never drinker)   Excess alcohol drinking is a well-established risk factor for breast cancer [30], besides being positively associated with anxiety and depression [31-33]. The most recent data on alcohol drinking habits prior to index date will be used in analysis. Current drinking will be further sub-divided into high, moderate, low or unknown intake of alcohol.   - Body mass index at diagnosis (categorical variable: underweight, normal weight, overweight, obesity class I, obesity class II and above)   Calculated as BMI=(weight/height^2^). Higher body mass index is protective against breast cancer in pre-menopausal women, but a risk factor for breast cancer post-menopause [34]. Obesity increases the risk of anxiety and depression [35, 36]. The most recent recording of BMI prior to index date will be used in analysis. The BMI values will be categorised into 5 categories: <18.5 kg/m^2^ (underweight), 18.5-24.9 kg/m^2^ (normal weight), 25.0-29.9 kg/m^2^ (overweight), 30.0-34.9 kg/m^2^ (obesity class I), ≥35.0 kg/m^2^ (obesity class II and above). Read codes for body weight categories recorded in the year prior to the breast cancer diagnosed will be considered to supplement missing information for this variable.   - Calendar period of diagnosis (categorical variable: ≤1994; 1995-1999; 2000-2004; 2005-2009; 2010-2014; >2014)   Even though calendar time *per se* does not change the risk of breast cancer, the risk of being diagnosed with breast cancer changed over time, probably due to increase awareness of the disease along with widespread use of mammography to screen for breast cancer. Time has also contributed for mental disorders being more likely to be diagnosed, due to raises awareness and increased recognition of the importance of mental disorders among health care professionals.   - Diabetes mellitus (dichotomous variable: yes/no)   Diabetes mellitus has been associated with an increased risk of breast cancer [37] and depression [38]. Algorithms previously defined elsewhere will be applied to identify patients with diabetes mellitus in the CPRD GOLD primary care database [39, 40].   - Level of deprivation (categorical variable: quintiles of patient-level IMD).   The IMD is an ecological measure of deprivation for small areas in England that combines information from seven domains (income, employment, education, health deprivation, crime, barriers to housing, and living environment), and ranks the small area from 1 (most deprived) to 32,844 (least deprived). Patients will be categorised in quintiles of IMD, with quintile 1 representing those least deprived and quintile 5 those most deprived.   - Menopausal status (dichotomous variable: premenopausal/postmenopausal)   Menopausal status is a potential confounder of the association between breast cancer history and depression, as the risk of breast cancer increases with menopause [30], and so does the risk of depression [42]. However, information on menopausal status is not easily available in the CPRD database. We will therefore produce results stratified by an age cut-off, as a proxy of the menopausal status of the women. The cut-off will be the mean/median age at natural menopause in the UK.   - Smoking history at diagnosis (categorical variable: current smoker, former smoker, never smoker)   Information on Read codes available on the data will be used to classify patients by smoking history. The most recent data on smoking prior to index date will be used in analysis. *Potential effect modifiers*  - Living alone (dichotomous variable: yes/no)   Ascertained from the CPRD GOLD primary care data using Read codes (list provided in [41]) and the patient’s family number (variable ‘famnum’ from the patient file). Women living in household of <2 people will be classified as living alone.   - Residing in a care home (dichotomous variable: yes/no).   This variable will be defined from the CPRD GOLD primary care database, using Read codes (list provided in [41]), and information gathered in the family number variable (‘famnum’). For the latter, ‘care home’ will be defined as a household with >3 individuals aged ≥65 years and if their total count was more than of individuals <65 years.   - Ethnicity (categorical variable: White, South Asian, Black, Others and mixed)   Ethnicity data recorded in the CPRD GOLD primary care database will be categorised in five groups, following the categories defined in the UK 2011 Census: White, South Asian, Black, Others and mixed. This variable will be derived from Read codes available in the CPRD GOLD primary care database and from HES, since the combined data sources increase completeness from 55% to 79% [41]. For analysis, four groups will be considered: White, South Asian, Black, Others and mixed.   - Previous mental health history (categorical variable: yes/no)   Mental health history will be defined as having had an episode of anxiety- or depression-related disorders (primary outcomes) or any the secondary outcomes, ever recorded at more than 1 year before the breast cancer diagnosis (patients who had the outcome in the year before the breast cancer diagnosis will be excluded from the cohort). These will be identified based on the algorithms defined in aim 1 of this study.   - History of stroke or coronary heart disease at diagnosis (two dichotomous variables: yes/no)   These will include ischaemic heart disease (angina and myocardial infarction) and stroke, which are amongst the leading causes of disability-adjusted life years in females in the UK. These will be identified through Read codes recorded in the CPRD GOLD primary care database.   - Socioeconomic status (IMD quintiles of deprivation)   The IMD is an ecological measure of deprivation for small areas in England (Lower Super Output Areas). It combines information from seven domain indices (income, employment, education, health deprivation, crime, barriers to housing, and living environment). The index ranks the areas from 1 to 32,844; usually the quintiles are used for research purposes: from 1 (most deprived) up to 5 (least deprived). The IMD is linked to the primary care data using the postcode of the patient or practice. *Potential mediators of the association between breast cancer history and anxiety/depression*  - Sequelae from cancer treatments (six separate binary variables (yes/no): lymphoedema, pain, mild cognitive impairment, fatigue, sexual dysfunction, sleep disorder)   Lymphoedema will be defined using Read codes for the condition, in the CPRD GOLD primary care database. Pain, mild cognitive impairment, fatigue, sexual dysfunction, and sleep disorder are secondary outcomes of this study, and will be identified based on the algorithms defined in aim 1 of this study. Patients will be classified as having had one of these conditions if there was more than one record for these conditions within a 6-month interval.   - Exposed to endocrine treatment for breast cancer: binary variable (yes/no).   This will be defined from the CPRD GOLD primary care database using Read codes for at least two prescriptions of anastrozole, tamoxifen, exemestane, or letrozole [43] within a 6-month period. |

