| Data/ Statistical AnalysisPrimary analysesSpecific aim 1. To develop and validate algorithms to identify patients with anxiety and depression Algorithm development  A systematic review is currently under way to identify the lists of Read codes previously used to define anxiety and depression of primary care databases in the UK. The systematic review search expressions are provided in appendix 5.  *(A) Raw data tabulations*  We will estimate the number and proportion of patients recorded during the observation period with:   1. Diagnostic Read code for anxiety/depression; 2. Prescription of anxiolytics/antidepressants; 3. Referred to mental health services; 4. Symptoms of anxiety/depression.   Proportions will be estimated by calendar year.  *(B) Simpler algorithm*  We will estimate the additional contribution of prescriptions, referrals and symptoms to identify cases of anxiety/depression in CPRD. Referrals and prescriptions of anxiolytics/antidepressants will be considered as sufficient to identify cases of anxiety/depression if a Read code for symptoms of anxiety/depression, respectively, were recorded during the previous year. The reasons for this are threefold: (1) there is good evidence that GPs switched from anxiety/depression diagnostic codes to symptomatic ones [44, 45], following claims of over diagnosis of these conditions; (2) antidepressants and anxiolytics have also other indications, including anxiety disorders for antidepressants [46], which raise questions of the use of these data their own to identify these outcomes; (3) pharmacological treatment of mild depression has been discouraged since 2004 [47], and thus referrals to psychotherapy may help to capture milder cases.  *(C) Complex algorithm*  A more detailed algorithm will be developed considering that some drugs are prescribed for both depression and anxiety, in addition to manage vasomotor symptoms, which may be more frequent in breast cancer survivors than in women who did not have cancer. An example for depression is given in appendix 6. We will estimate the number of patients with anxiety/depression at each step, to evaluate how much each category adds to what has been previously recorded.  Algorithm validation  A random sample of 1 million patients of both sexes will be selected from the CPRD GOLD primary care database. We will apply each algorithm and produce descriptive statistics stratified by likelihood of having the outcome, including:   - Number and proportion of patients with the anxiety, depression or both, by 3-year calendar period; - Number and proportion of patients with the anxiety, depression or both, by 3-year calendar period, age and sex; - Number and proportion of patients with the anxiety and depression by 3-year calendar period and country in the UK.   For each outcome, we will compare the estimates obtained with others obtained from the literature, prioritising national surveys of population-based data such as the following:   - Adult Psychiatric Morbidity Survey 2007 [48] and 2014 [49]; - Measuring National Well-being programme, made available by the Office for National Statistics (includes prevalence of those in the UK with some evidence indicating depression or anxiety, since 2013, by country in the UK and English regions, and by 10-year age groups up to 75 years) [50].   The final algorithm will be chosen by considering information in the numeric value closer to the estimates obtained from the literature. Sensitivity analysis Proportion estimates considering the presence of symptomatic codes within the previous year will be re-calculated to consider shorter periods of time (i.e. 3 and 6 months). Specific aim 2. Risk of mental health outcomes in women who had breast cancer compared to women who did not have cancer**Primary outcomes analysis – depression and anxiety**Main analysis Descriptive statistics including number of events observed and person-years at risk will be computed, overall and stratified by the covariates listed in section M (see above). Medical procedures for the diagnosis of breast cancer are likely to cause anxiety. To deal with this we planned to exclude patients who had a record of anxiety diagnosed within 1 year before the breast cancer; this could result in patients with higher levels of trait anxiety being excluded from the analysis. We will calculate the number and proportion of patients who were excluded because they had the outcome in the year prior to the breast cancer, stratified by month. We will also describe how many of those who were excluded from analysis had an outcome after the breast cancer diagnosis by age-group. The quintiles of the distribution of the number of consultations (defined using the ‘consid’ variable) will be described, as this can indicate the patterns of seeking care between women with a history of cancer, compared to those who did not.  The association between breast cancer history and anxiety and breast cancer history and depression, will be quantified using Cox regression models with time since index as the underlying time scale, and stratifying on matched set to account for matching by age and primary care practice. Follow up will begin at the index date (vide section M for definition of the exposure) and will terminate when an outcome is observed. Women will be censored at the earliest date of any of these: cancer recurrence, other cancer diagnosis, death, transference out of the practice; if these events don’t occur, censoring will be observed at the date of last data collection for the practice. Crude measures of the association between breast cancer history and anxiety and depression will be reported stratifying by the covariates described in section M.  Cox multivariate regression analysis will be use to estimate hazard ratios adjusted for calendar period of breast cancer diagnosis, menopausal status, and diabetes mellitus at baseline (see list of confounders in section L, covariates, for the definition of these variables).  Interaction terms between the exposure and the following variables will be added, to explore effect modification by ethnicity (White, South Asian, Black, Others and mixed), place of residence (care home vs. household), co-habitation status (living alone vs. cohabiting), SES (quintiles of IMD), having mental health disorders history (yes vs. no), having history of stroke (yes vs. no) and coronary heart disease (yes vs. no).  Confidence intervals will be calculated using robust estimates of the standard errors, to account for the fact that patients may also contribute with time at risk in the unexposed cohort prior to their cancer diagnosis.  The proportional hazards assumption will be tested in two ways: 1) graphically, by plotting the cumulative rates on a log scale; 2) inferentially, by applying a likelihood ratio test to the estimates obtained for the entire period of observation and for time split into intervals. Sensitivity analyses Sensitivity analyses planned for this study will include a subset of patients only; this is because they use variables from linked data, which is available for a fraction of the patients only, and include variables amenable to have missing data (i.e. BMI, alcohol intake, smoking and patient-level IMD). Regarding the latter, we will quantify the completeness of each variable to decide on their inclusion in the final models. Analyses including variables with missing data will be restricted to patients with complete data for covariates (complete case analysis), if missing data is likely to be missing not a random. The following sensitivity analyses are planned:   1. The main analysis will be repeated further adjusting for age at diagnosis (continuous variable, since matching allowed for 3-year gap), patient quintile level of IMD, alcohol drinking patterns prior to index date, smoking history and body mass index categories prior to index date. 2. We will exclude women diagnosed with the outcome of interest in the year prior to the cancer diagnosis. To account for the fact that treatment for these conditions may often last for more than one year, and that mild anxiety and depression may be treated in psychological services and not result in visits to the GP, we will repeated the main analysis including only patients who had 5 years of complete follow up prior to the index date and did not have the outcome recorded at any point during this period.  Multiple comparisons We acknowledge that this study includes multiple comparisons for each outcome, and several outcomes. Thus, P-values in the range ~0.01-0.05 be considered as some statistical evidence of an effect and interpreted cautiously. Sample size considerations considering a 0.01 probability of type I error (α) are provided in see section I. Specific aim 3. To estimate association between breast cancer history and anxiety/depression by presence of lymphoedema, pain, mild cognitive impairment, fatigue, sexual dysfunction, sleep disorders, and having done endocrine therapy, during the follow up period. We will estimate the cumulative incidence and period prevalence of lymphoedema, pain, mild cognitive impairment, fatigue, sexual dysfunction, and sleep disorders, in breast cancer survivors during the overall follow up period and by 5-year of follow up period.  We will estimate the hazards of developing anxiety and depression (the main outcomes) for three groups of patients: 1) breast cancer survivors who did not develop the common complication (i.e. lymphoedema, pain, mild cognitive impairment, fatigue, sexual dysfunction, sleep disorders) up to time *t*; 2) breast cancer survivors who have had the common complication at time *t*; 3) women who never had cancer. A Cox regression model will be used to estimate the association between time-updated exposure and the main outcomes (anxiety and depression), having as reference the hazard observed for the women who did not have cancer. The exposure variable will be time-updated; this means that women who develop a common complication will contribute with information to group 1 until the date at which they develop the complication of interest; after this point they will contribute with information to group 2. All models will be adjusted for calendar period of breast cancer diagnosis.  Confidence intervals will be calculated using robust estimates of the standard errors. Sensitivity analyses planned in objective 2 will be applied to this objective as well. Secondary outcomes analyses – fatigue, mild cognitive impairment, pain, sleep disturbance, sexual dysfunction, fatal and non-fatal self-harm The steps outlined above will be repeated for the secondary outcomes. Sensitivity analysis will follow the same rationale as described for the primary analysis. |

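### The two end-of-follow-up rules do not match, and censoring only survivors at recurrence makes the main HR describe time before recorded recurrence, not all survivorship

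*Protocol*

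**What the plan says.** Two sections of the protocol fix the end of follow-up.

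- Study Design: all women are "followed from the index date until the earliest date of: outcome observed, a cancer diagnosis, death recorded, transference out of the practice", or until the practice's last data collection. Recurrence is not named.
- Data/Statistical Analysis, Specific aim 2, Main analysis: "Women will be censored at the earliest date of any of these: cancer recurrence, other cancer diagnosis, death, transference out of the practice", again with last data collection as the final limit. Recurrence is named, separately from other cancers.

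Three further statements bear on how these rules act.

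- Comparison women are selected "with no history of cancer at the index date". The same section adds: "Women diagnosed with breast cancer during the follow up period will be censored from the unexposed group at the date of the cancer diagnosis". They may then enter the exposed cohort.
- Exposure starts at the index breast cancer, "denoted by the first entry of one or more of the Read codes provided in appendix 2".
- The Cox model uses time since index, "stratifying on matched set to account for matching by age and primary care practice".

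The main analysis lists two sensitivity analyses: one adds covariates, the other requires five outcome-free years before index. Neither changes the censoring rule. The steps are to be repeated for every secondary outcome, including self-harm and suicide.

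**The concern.** The two rules can produce different datasets. The Study Design wording could cover recurrence, could mean new cancers only, or, read literally, could let any later breast cancer code end a survivor's follow-up. The analysis section settles on recurrence plus other cancers.

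The analysis rule also does different things in the two arms. For a comparison woman, a first cancer means she no longer belongs to the cancer-free group, so ending her follow-up is natural. A survivor whose cancer recurs is still a survivor, and recurrence is a consequence of the exposure. The protocol treats other consequences differently: under Specific aim 3, women who develop lymphoedema, pain, fatigue and similar sequelae stay in follow-up with a time-updated exposure. No reason is given for treating recurrence otherwise.

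At stake is what the main HR means. A small HR that applies before recorded recurrence could be read as an answer for all survivors, which is how the title, general objective, null hypothesis and study population frame the question.

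**Working it through.** The protocol states no figure to reproduce on this point. The check has three parts.

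**1. Who can be censored, and for what**

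| Event after index | Survivors | Comparison women |
| --- | --- | --- |
| Recurrence | Censored (Main analysis); unclear (Study Design) | Cannot occur: cancer-free at index, and follow-up ends at first cancer |
| Other or first cancer | Censored | Censored |
| Repeat code for the index cancer | Not addressed; could count as a cancer diagnosis under Study Design | Not applicable |

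**2. What the censored model estimates**

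Each matched set has one exposed woman. Once she is censored, only unexposed women remain in the set's risk sets, and these carry no information on the exposure effect. Shortened survivor follow-up is therefore not set against full-length comparison follow-up. The model gives an HR for time before recorded recurrence.

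**3. How far that could lie from an HR over all survivorship**

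All inputs are assumptions. HR0 = 1.20 is the HR before recurrence, p is the share of survivors' person-time after recurrence, and HR1 is the HR against comparison women after recurrence.

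Approximation: HR(all) = HR0 × (1 − p) + HR1 × p.

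- Smallest rise: 1.20 × 0.98 + 1.5 × 0.02 = 1.206.
- Largest rise: 1.20 × 0.92 + 3.0 × 0.08 = 1.344.

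| p | HR1 = 0.96 (hazard falls) | 1.20 (unchanged) | 1.5 | 2.0 | 3.0 |
| --- | --- | --- | --- | --- | --- |
| 2% | 1.195 | 1.200 | 1.206 | 1.216 | 1.236 |
| 5% | 1.188 | 1.200 | 1.215 | 1.240 | 1.290 |
| 8% | 1.181 | 1.200 | 1.224 | 1.264 | 1.344 |

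Against 1.20, the rise runs from 0.006 to 0.144.

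A simulation of 1:4 matched sets, analysed by Cox regression stratified on set, checks this. Its assumptions are an outcome rate of 1.5 per 100 person-years in comparison women, a true HR of 1.20 before recurrence, death at 25% per year after recurrence, and follow-up of up to 10 years. Here m is the hazard after recurrence relative to before. Cells show the HR censored at recurrence, then not censored.

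| Recurrence per year | m = 0.8 | 1 | 1.5 | 2 | 3 |
| --- | --- | --- | --- | --- | --- |
| 1% | 1.208, 1.204 | 1.206, 1.204 | 1.198, 1.210 | 1.213, 1.230 | 1.206, 1.245 |
| 3% | 1.200, 1.185 | 1.222, 1.220 | 1.218, 1.244 | 1.198, 1.253 | 1.210, 1.323 |

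Simulation error is about 0.01 to 0.02 per estimate. The censored HR stays near 1.20 whatever m is. The uncensored HR rises when m exceeds 1, barely moves at m = 1, and dips when m is below 1.

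**The case against.** The strongest defence is that an HR before recurrence is a legitimate quantity, and perhaps the intended one. The lay summary speaks of mental health some years after treatment, and the rationale concerns the long term. With stratification on matched set, one-sided censoring does not by itself distort that HR. This stands, so the censored analysis is not an error in itself. But the protocol never says that this is the target. Its follow-up starts at diagnosis, and its study population is every adult woman with incident breast cancer.

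It can also be said that the Study Design wording is shorthand for the fuller rule. That is possible, so this is an unresolved mismatch rather than a flat contradiction.

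A reader might infer that the rule discards survivors' most distressed period. The documents do not support this: they say nothing about outcomes after recurrence, and the Study Background reports the highest risks soon after diagnosis, a period that is retained.

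A reader might also infer that recurrences will be badly captured, from the sentence "Information on the exposure will not be supplemented by data from HES-APC" and from appendix titles that do not mention recurrence. That sentence concerns exposure, the appendix contents are not shown, and code lists may sit in a statistical analysis plan. The missing definition is therefore not counted here. Any recurrences left unrecorded would stay in follow-up and make the shift smaller.

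Finally, the illustrated shift should not be set directly against the UK ratios of 1.06 and 1.08 in Table 2. That study covered women at least five years after diagnosis and reported odds.

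**Conclusion.** The point holds as a mismatch between two rules and an undeclared target. Under the analysis section the main HR applies to survivors before recorded recurrence, the stated question covers all survivors, and no listed analysis shows the difference.

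It would be tempting to conclude that the HR is biased downwards. That requires two conditions the documents do not establish: that the target is all survivorship, and that the outcome hazard rises after recurrence. The second is plausible but undocumented. If both hold, the reported HR is too low by about 0.01 to 0.14 on a base of 1.20. This assumes 2% to 8% of survivors' person-time falls after recurrence, with an HR of 1.5 to 3.0 there. If the hazard is unchanged there is no shift, and if it falls the reported HR is slightly too high. For scale only, the smallest detectable ratios printed in Table 2 for the primary outcomes run from 1.02 to 1.11.

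This is a worthwhile, inexpensive improvement and does not show that the planned analysis is invalid.

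**What to change.** 1. Write one end-of-follow-up rule and use it in both Study Design and the Specific aim 2 Main analysis.
2. State that a repeat code for the index breast cancer does not by itself end an exposed woman's follow-up.
3. State whether the main HR refers to survivors without recorded recurrence or to all survivors. Either can be the main analysis if it is declared.
4. For each outcome, report a second Cox model stratified on matched set in which exposed women are not censored at recurrence and comparison women are still censored at first cancer. Label the two results by the population each describes.

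The cost is protocol wording and one extra model run per outcome on data already held. The downside is that the uncensored HR mixes time before and after recurrence, so it should be read beside the censored one.
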